### Monitoring, ethical considerations, and safety

The group leaders record each session so that the study employees can randomly examine the adherence to the intervention manual. In addition, the group leaders document each session (e.g. attendance, mood of participants, disturbances) and contact participants individually via the study online portal in the case of absence, problematic behavior, suicidality, or deterioration of symptoms. In addition, the study employees receive an automatic email when participants report increased levels of suicidality in the questionnaires after each session. If suicidality or adverse effects are suspected, the study employees will call the participants once a week to monitor and assess their mood and offer support.

The randomized controlled trial was approved by the ethics committee of Medical School Hamburg (03.03.2018). Participants are informed in writing (i.e. study information, consent form) about the procedure of the program, the aims of the study, the inclusion and exclusion criteria, risks and costs of participation, confidentiality, and data storage. They have the opportunity to drop out of the program at any time without giving reasons. They are also allowed to use other assistance (e.g. psychotherapy) in addition to study participation.

The participants are also informed about the possibility of detecting abnormalities in the clinical interview (before treatment) or during the data analysis. In that case, we contact participants for a more detailed clinical assessment. If we find clinically relevant aspects or diagnoses, the participants will be informed. However, we point out that study assessments do not substitute clinical diagnosis by a medical doctor or psychotherapist.

During treatment, participants may experience a worsening in mood and sadness at first when they deal with the suicide of their loved ones. Such mood aggravations are normal in an intensive grief process and usually exist only for a short time. In the case of acute suicidality (i.e. corresponding hints in the suicidality item of the BDI-II), we contact the participant by telephone and offer counseling. He or she may be excluded from the program and referred to local professionals. However, the scientific evidence so far suggests that the proposed online program can reduce difficulties in coping with grief reactions and symptoms. Hence, we do not expect any unwanted side effects or lasting psychopathological worsening at the end of the program. Additionally, a supervisor will provide clinical supervision every fourth session to ensure treatment adherence and provide clinical support.

There will be no external data monitoring committee because the Sponsor and cooperation partners will function whereby procedures, results, and modifications have to be communicated on a regular basis (at least twice annually). Although the execution of the study and the data analyses are independent of these institutions, we will write several interim reports about the achievement of project aims, results, and finances and justify deviations. If adverse events arise in the suggested procedures (e.g. eligibility criteria, randomization strategy, parts of the intervention, etc.) the study coordinators will discuss the necessity and impact of possible changes to the study protocol. An audit is not scheduled in our study.

## Discussion

The primary aim of the study is to reduce suicidality and depression in people bereaved by suicide, using an online-group intervention. Furthermore, the intervention aims to reduce secondary parameters such as prolonged grief, anxiety, or PTSD. Last but not least, we are also interested in sociodemographic predictors (e.g. age, sex, relationship to the deceased) that predict successful treatment and in the cognitive processes (e.g. experience of stigmatization, guilt) that influence the participants’ general psychopathology.

People bereaved by suicide have a high risk of developing mental illnesses and committing suicide themselves [10]. For this reason, it is important to provide adequate low-threshold support. One of the main advantages of the program is that it is easy to access and geographically independent. The attendance of the participants and the group leaders is possible without much technical knowledge and without any special equipment. Furthermore, participants can largely remain anonymous, which might decrease hesitation to seek professional help, as after suicide people often face stigmatization in their environment. The advantages mentioned above also apply to the group leaders. Further, the intervention offers the unique opportunity to meet other people after suicide bereavement, which reduces social isolation.

With a planned sample size of more than 70 participants, this trial is adequately powered for detecting a medium effect size for the comparison between the treatment and the waitlist group. Additionally, we explore multiple predictors of treatment-outcome moderator variables to define detailed processes of the effectiveness.

The study has multiple methodological strengths such as block randomization and the use of a standardized manual with precise procedures and instructions that are based on cognitive behavioral principles. The group leaders receive detailed training and regular supervision to ensure treatment fidelity. Because the intervention is led by a psychologist and a self-help counselor who has also experienced suicide loss, both perspectives are considered, thus complementing each other’s work. Last but not least, this study uses validated questionnaires and an additional clinical interview in the diagnostic process to make sure the participants meet the inclusion criteria.

Despite its strength, some limitations of the current study design are worth mentioning. First, the study does not test whether the online group intervention is more effective than standard psychotherapy or self-help groups, because we use a waitlist control group design. Future research should expand this approach to active treatment conditions. Second, the organization of groups is not always without difficulties (e.g. temporary delays, schedule difficulties). This could mean that participants have to be randomized a second time if they cannot take part in the assigned group appointment. Further, participants may seek professional support in addition to our program. This might affect the effect sizes of our intervention although we control for such influences (e.g. record additional psychotherapy, medication, self-help groups). Follow-up studies or dismantling studies might further investigate which aspects of the intervention in particular drive the effects.

Taken together, this study and its results will help to better understand the problems faced by people bereaved by suicide. We expect our online group intervention to be effective in reducing parameters like depression, suicidality, and prolonged grief disorder. Hopefully, the knowledge thus gained can be used for further studies in this target group.

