### Trial design

This study is a randomized control group design with two groups of equal sample size: the treatment group and the waitlist control group. The treatment group will receive treatment through the online group intervention immediately after registration. As a result of the focus groups with suicide survivors, the waitlist control condition was selected as the only one acceptable to the suicide survivors involved. A control that would not receive the intervention after the waiting period could reduce the motivation to participate.

This intervention is based on cognitive behavioral principles (psychoeducation, cognitive restructuring, dealing with difficult emotions such as guilt, shame, suicidality) and will take place once a week over a course of 12 weeks in total. The waitlist control group will receive the same intervention 12 weeks after registration. Participants will be randomly assigned to either group using computer-generated block-randomization. The study protocol was written in accordance with Statement Standard Protocol Items: Recommendations for Interventional Trials (SPIRIT) 2013 [33]; for the SPIRIT Checklist see Additional file 1).

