### Randomization

We will use block randomization without extra stratification: As soon as 10 participants are included, they are considered to form a group. A researcher (first author) who is not involved in participant recruitment, clinical assessments, or treatment, obtains the information by e-mail that a new group is complete. Then, the whole group is randomly assigned to either the treatment or the waitlist control group. The researcher then executes the randomization using a generated list at www.random.org. The person who is allocating the participants thus has no influence on the randomization and enrollment process. Following randomization, participants will be notified of their allocation.

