### Blinding

Because of the high level of organizational effort involved in randomizing groups, it is not possible to blind the participants, group leaders, or study employees. The data analysis will be blinded. Thus, an independent researcher will conceal the participants’ IDs and their group assignment in the data set (i.e. relabel the variables). After all results are finalized, the independent researcher will reveal the correct group identification to the authors.

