### The online group intervention

The online group intervention is manualized and consists of 12 weekly sessions each lasting 90 min. Each group has a maximum of 10 participants and is guided by a psychotherapist (or a psychotherapist in training) and a self-help counsellor who has herself or himself been bereaved by suicide. The participation is voluntary and free. Participants are allowed to skip sessions or to drop out of the program at any time.

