### Handling of missing data

We will follow the principles of intention-to-treat analysis. Participants who drop out of the study after randomization are asked to state their reasons for doing so and are asked to continue the assessments. Missing values will be imputed using the approach of last observation carried forward. In the case of a participant dropping out during the intervention, the participant will be asked to fill in the post-questionnaire, and the reason for dropping out will be assessed.

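### The article allows a second randomisation after the arm is known and does not reconcile it with the intention-to-treat commitment

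*Protocol article*

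**What the plan says.** The Randomization section of the protocol article forms a group once 10 participants are included. "Then, the whole group is randomly assigned to either the treatment or the waitlist control group". A researcher outside recruitment, assessment and treatment makes the draw from a generated list. The section ends: "Following randomization, participants will be notified of their allocation". It contains no rule for redrawing anyone.

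Under Blinding, the article states that "it is not possible to blind the participants, group leaders, or study employees"; only the data analysis is blinded. Under Trial design, the treatment group starts at once after registration, while for the other arm: "The waitlist control group will receive the same intervention 12 weeks after registration".

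The Discussion, among the limitations, mentions delays and scheduling difficulties in organising groups and adds: "This could mean that participants have to be randomized a second time if they cannot take part in the assigned group appointment". It does not restrict the second draw to the same arm, to the time before notification, or to a single repeat.

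Handling of missing data commits to the analysis principle: "We will follow the principles of intention-to-treat analysis". It continues: "Participants who drop out of the study after randomization are asked to state their reasons for doing so and are asked to continue the assessments". The online group intervention section already tolerates non-attendance: "Participants are allowed to skip sessions or to drop out of the program at any time".

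**The concern.** A second draw is harmless only if the reason for it has nothing to do with the result of the first. Here the trigger is an inability to attend a particular appointment, and the appointment depends on the arm. A weekly slot starting now and one starting 12 weeks after registration clash with people's lives in different ways. Availability may also be related to motivation, distress or working status, and so to depression and suicidality, the two primary outcomes.

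Two things are at stake. The first is comparability: if the replacement arm is the one analysed, membership of an arm depends partly on an event after allocation that can differ between arms. The second is the unit of randomisation. The scheme allocates intact groups, and the Statistical analysis section plans multilevel models around them. A person redrawn alone leaves the group that was randomised, and the article does not say how that person re-enters a scheme that draws only whole groups.

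**Working it through.** The plan states no redraw rate and no figure for the effect of redraws, so there is nothing of its own to reproduce. The check has two parts: the order of events, then a range under stated assumptions.

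**1. Is the arm known when the redraw happens?** Randomization has participants notified after the draw. The Discussion makes the redraw conditional on being unable to attend the assigned appointment, and a person can report that only after learning of it. So the redraw comes after the arm is known.

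**2. Which allocation is analysed?** No section says. Both readings are worked through below.

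Inputs from the Sample size section: 52 per arm, d = 0.80, 30% dropout. Assumptions: the second draw is 1:1; redrawn people receive what the second draw gives them; where prognosis matters, they differ from the rest by 0.5 SD.

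**3. Second allocation analysed, redraws in the treatment arm only.** Let a share q of each arm be people who could not make an immediate slot. Only those in the treatment arm are redrawn, and half of them move.
- Treatment arm: size 52 × (1 − q/2), share of such people (q/2)/(1 − q/2).
- Waitlist arm: size 52 × (1 + q/2), share (3q/2)/(1 + q/2).
- Bias with no true effect = 0.5 × difference in shares.

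| q | Arm sizes (treatment / waitlist) | Shares | Difference | Bias (SD) |
|---|---|---|---|---|
| 10% | 49.4 / 54.6 | 5.3% / 14.3% | 9.0 points | 0.045 |
| 20% | 46.8 / 57.2 | 11.1% / 27.3% | 16.2 points | 0.081 |
| 30% | 44.2 / 59.8 | 17.6% / 39.1% | 21.5 points | 0.107 |

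The size is the same if only the waitlist arm is redrawn. The sign depends on which arm is redrawn and on whether those people have the better or worse prognosis, neither of which is known. Relative to the design effect, 0.045/0.80 = 6% and 0.107/0.80 = 13%.

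**4. Second allocation analysed, equal redraws of similar people in both arms.** Each arm loses and regains the same expected number, the shares stay equal, and the expected bias is zero.

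**5. First allocation analysed.** Half of the redrawn people cross over, so the expected d = 0.80 × (1 − (qT + qC)/2), where qT and qC are the shares redrawn in the treatment and waitlist arms. With equal shares:
- 5%: 0.80 × 0.95 = 0.76
- 10%: 0.80 × 0.90 = 0.72
- 20%: 0.80 × 0.80 = 0.64

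With 52 × 0.7 ≈ 36 evaluable per arm and clustering ignored, power from the normal approximation Φ(d√(n/2) − 1.96) is 0.92 at d = 0.80, and 0.90, 0.86 and 0.78 at these three values. This reading is valid as intention-to-treat but loses power.

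**The case against.** The sentence is a disclosed, conditional limitation and not a rule in the Randomization section. A reader might infer from it three stronger things that the article does not support.

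- *That it contradicts intention-to-treat.* This would follow only if the second allocation were analysed, and no section says so. Keeping the first allocation would be compatible with the commitment.
- *That participants select their own arm*, for example that a waitlisted person gains a second chance of immediate treatment by declaring a conflict. The stated trigger is inability to attend, and nothing says that a bare declaration is enough. A redrawn person cannot choose the new arm. At most, a participant influences whether a redraw happens.
- *That no analysis could deal with the bias.* The Statistical analysis section plans ANCOVA on baseline depression and suicidality, which would reduce the part of the bias carried by those variables, though not a part due to unmeasured motivation or availability.

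The assumed shifts are also small beside d = 0.80, and they need redraw rates, or the kind of person redrawn, to differ by arm. The documents make that plausible but do not show it.

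All of this stands, and it limits the severity. It does not remove the point. Disclosure adds no safeguard, and under either reading the redraw costs something: possible bias or dilution. The article also sets a post-notification individual redraw beside a group-level scheme and an intention-to-treat commitment without connecting them.

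**Conclusion.** The point holds as an unreconciled provision that should be fixed. Followed as written, it lets the final allocation depend on an event after notification that can differ by arm, and it detaches individuals from the randomised group. If the second allocation is analysed, the result is not intention-to-treat and may be biased by about 0.05-0.11 SD, in an unknown direction, assuming that 10-30% of one arm only is redrawn and differs by 0.5 SD. If redraws are equal in rate and kind across arms, the expected bias is zero. If the first allocation is analysed, d falls from 0.80 to 0.76-0.64 for 5-20% redrawn in both arms. All rates and the 0.5 SD are assumptions. These figures do not show a fatal flaw. The reason to act is that the protection given by randomisation is weakened for no gain that a same-arm move could not largely supply.

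**What to change.** Remove the second randomisation, or ask each prospective group about availability for both possible start dates before it is randomised. In either case:

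- Keep and analyse every participant under the first allocated arm and the first-randomised group.
- Allow a move only to another group of the same arm. If none is available in time, count the participant as a non-attender and assess on the original schedule.
- For anyone already redrawn, recover the first allocation and report the number by arm. This must happen before the coding list described under Personal data is destroyed, which is due after data collection.
- Add a sensitivity analysis by group attended.

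The protocol version is dated 21.10.2019 and recruitment was to run until about May 2020, so the rule could still be changed at that version.

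The cost is more than a change of wording. With 104 participants in groups of 10 there are about ten groups, over roughly 19 months from October 2018. If evenly spaced and split between arms, a group forms about every 1.9 months and one of the same arm about every 3.8 months, or some 16 weeks. It may also be full, because groups are capped at 10. Some participants would therefore wait for a later group or remain untreated at the 12-week assessment, which dilutes the effect slightly. Settling availability before the draw avoids most of this, at the price of somewhat slower group formation.

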## Dissemination

We will present the results of the study to the scientific community in peer-reviewed journals and at international and national conferences. We will report the results to the non-scientific community by publishing them on our website, in newspaper articles, in newsletters for VEID and AGUS, and in magazines for practitioners. Participants interested in the study results will receive a report via email.

## Trial status (version 1 19/08/2019)

We started recruitment in October 2018.

Recruitment will be finished approximately by May 2020.

## Data Availability

The datasets generated and/or analyzed during the current study are available from the corresponding author on reasonable request.

## Abbreviations

ACSS-FAD: Revised Acquired Capability of Suicide Scale
AGUS: Angehörige um Suizid e.V.
BDI-II: Beck Depression Inventory-II
BPD: Borderline personality disorder
BSS: Beck Scale for Suicide Ideation
BSSS: Berlin Social Support Scales
GEQ: Grief Experience Questionnaire
GQ: Group Questionnaire
H-Scales: Hopelessness Scale
ICG-D: Inventory of Complicated Grief-German Version
IES-R: Revised Impact of Event Scale
PHQ-D: Short Version of the Patient Health Questionnaire-German Version
PTCI: Posttraumatic Cognitions Inventory
PTSD: Posttraumatic stress disorder
QPDDN: Questionnaire on Police Delivery of Death News
SkPTBS: Screening for complex posttraumatic stress disorder
SPIRIT: Standard Protocol Items: Recommendations for Interventional Trials
STOSASS: Stigma of Suicide and Suicide Survivor
VEID: Bundesverband Verwaiste Eltern und trauernde Geschwister e.V.
